## Abstract

**Background:**

Antibiotic resistance (ABR) is a global health threat, significantly driven by its misuse. The World Health Organization stresses the need for better antibiotic use to combat ABR through behavioral change interventions. Visual storytelling, which merges narrative with visuals, can enhance health behaviors by boosting cognitive and emotional engagement. In Pakistan, more than half of the population lack access to mobile phone, limiting digital health solutions. To address this gap, we developed a culturally tailored Visual Storytelling for Antibiotic Adherence (VISTA) intervention – a theory-driven sticker-based tool – to improve antibiotic adherence among urinary tract infection (UTI) patients in low-connectivity settings.

**Methods:**

In this parallel, two-arm superiority randomized controlled trial, participants with physician-confirmed uncomplicated UTI who have filled an oral antibiotic prescription will be recruited from six tertiary care hospitals in Khyber Pakhtunkhwa, Pakistan. The participants will be randomized in a 1:1 manner to receive either the VISTA intervention or standard care. The VISTA intervention was developed based on nudge theory, guided by the Taxonomy of Choice Architecture framework, and complemented by the MINDSPACE (messenger, incentives, norms, defaults, salience, priming, affect, commitments, and ego) framework. It was developed and validated through a Delphi method, assessing expert feedback, and refined based on a patient understanding study. The intervention sticker uses contrasting colors—red (non-adherence: bacteria evolving into “superbugs”) and green (adherence: antibiotics fully eradicating bacteria)—to communicate the consequences of incomplete versus complete adherence. The primary outcome is adherence, measured by pill count at the initial follow-up. Secondary outcomes include UTI recurrence, knowledge, and attitudes regarding antibiotic adherence. Analysis will follow both intention-to-treat and per-protocol principles.

**Discussion:**

This randomized controlled trial will evaluate a theory-driven, scalable intervention for low-resource, low-connectivity settings, aligning with WHO priorities for ABR mitigation. It addresses the patient support gap caused by limited digital access. Pill counts provide an objective adherence measure, though they may miss intentional non-adherence; including UTI recurrence as a secondary outcome helps mitigate this. Cultural tailoring through expert panels and patient feedback aims to enhance relevance and applicability across similar contexts, improving generalizability.

**Trial registration:**

The trial was registered with ClinicalTrials.gov (registered: March 13, 2025, NCT06885658, https://clinicaltrials.gov/study/NCT06885658).

**Supplementary Information:**

The online version contains supplementary material available at 10.1186/s13063-025-09328-1.

## Introduction

### Background

Antibiotic resistance (ABR) presents significant global public health threats, and it is estimated that antibiotic-resistant infections will lead to 10 million deaths each year by 2050 [1]. The overuse and misuse of antibiotics play a significant role in the development of ABR [2–4]. Antibiotic misuse from the demand side includes practices such as obtaining antibiotics without a prescription, self-medication, and failing to adhere to the prescribed treatment, which involves skipping doses or not completing the antibiotic course [5, 6]. To combat the impending threat of ABR, the World Health Organization (WHO) has identified improving rational antibiotic use among individuals as the most essential policy target to mitigate ABR [7].

Non-adherence to antibiotic therapy, a pervasive yet comparatively under-prioritized form of misuse, constitutes a major ABR driver. This behavior stems from multifaceted barriers including forgetfulness, regimen misunderstanding, insufficient awareness about the consequences of incomplete treatment [6, 8], premature discontinuation upon symptom relief, or dose omission due to side effects or financial constraints [6, 9], and comprehension challenges among individuals with limited health literacy, particularly in resource-poor settings [9, 10]. Studies confirm that non-adherence accelerates resistance evolution, as incomplete treatment courses enable bacterial survival and select for resistant strains, progressively eroding antibiotics’ efficacy [11, 12]. Thus, enhancing patient adherence to prescribed antibiotic regimens aligns with WHO’s individual-focused mitigation strategy and is essential to preserve therapeutic effectiveness.

To address these behavioral challenges, our intervention leverages “nudge” theory advocated by Thaler and Stain in 2008, which is a framework proposing that subtle choice architecture modifications can predictably influence decisions while preserving autonomy [13]. While prior nudges primarily targeted prescriber behavior, for instance, social norm feedback reducing antibiotic prescriptions [14], we apply this approach to patient adherence. Specifically, we employ visual storytelling—a nudge-aligned technique using narrative and visual cues to guide antibiotic adherence decisions. This approach has proven effective in fostering adherence behavior by engaging both cognitive and emotional pathways, thus enhancing the patient’s understanding of antibiotics and encouraging actions that mitigate resistance [15–17]. Moreover, visual storytelling can help to overcome socioeconomic barriers in low-resource settings by offering a cost-effective way to educate patients about the risks of ABR and the importance of completing prescribed antibiotic courses. This ultimately contributes to improved health outcomes and reduced resistance rates [18].

### Rationale and research question

Visual storytelling enhances antibiotic adherence by cognitively and emotionally engaging patients, transforming complex medical information into more accessible and memorable visual narratives. By combining narrative elements with visual cues, visual storytelling helps patients understand causal relationships between non-adherence and consequences, including ABR and treatment failure, and highlights the importance of completing their prescribed antibiotic courses, which is crucial in preventing ABR [17]. Additionally, emotional involvement fosters empathy or concern, motivating patients to adhere more closely to their treatment regimens [19].

In low-resource settings, where digital strategies, such as Short Message Service (SMS) and smartphone applications, face limited feasibility given disparate mobile phone and smartphone access, visual storytelling provides an important solution that is scalable and affordable [20, 21]. Notably, while mobile phone ownership is 78% in LMIC [22], in Pakistan, only 46% of the population owns a mobile phone, and this rate is even lower in rural areas and for smart phone ownership [23]. By emphasizing non-digital methods, the intervention ensures inclusiveness for over half the population without mobile phone access, addressing systemic healthcare inequalities.

Visual storytelling’s ability to simplify and visualize complex medical information and arise emotional responses holds potential for fostering long-term behavioral changes, particularly in populations with limited access to digital tools. This approach aligns with the need to address antibiotic adherence disparities in resource-constrained settings. While storytelling has been effectively applied in domains like vaccination promotion [8], improving psychological outcomes [9–12], and management of anxiety in cardiac ICU [13] and dental pain [24], its potential to improve antibiotic adherence remains unexplored.

As such, this current study will employ a randomized controlled trial (RCT) design to evaluate whether a sticker-based Visual Storytelling for Antibiotic Adherence (VISTA) intervention improves antibiotic adherence compared to standard care among adults with uncomplicated urinary tract infections (UTIs). Our research question's feasibility, significance, novelty, ethical considerations, and relevance are framed according to the FINER criteria.

## Method

The protocol was reported in accordance with Standard Protocol Items: Recommendation for Interventional Trials (SPIRIT) [25].

### Study design

The study will employ a parallel two-arm superiority RCT design to test whether the VISTA intervention results in higher antibiotic adherence than standard care. Participants will be randomly allocated in a 1:1 ratio to either the intervention group or the control group. For the control group, participants will receive routine care, typically verbal or written instructions about antibiotic use, because it reflects the real-world standard practice for UTI treatment in Pakistan, whereas the intervention group will include VISTA stickers on the antibiotic boxes to improve antibiotic adherence. Both groups will be monitored for their adherence to the prescribed antibiotic course. The details can be seen in Fig. 1.

**Fig. 1 Fig1:**
[figure not shown]
Schematic flow diagram of the trial. ITT intention-to-treat analysis, PPA per-protocol analysis

### Study setting

The study setting will be tertiary care hospitals in the Khyber Pakhtunkhwa province of Pakistan. According to the health department of Khyber Pakhtunkhwa, there are nine tertiary care hospitals (healthkp.gov.pk/#). For this study, six hospitals were selected based on their willingness to participate and support the research (Peshawar, *n* = 3,; Swat, *n* = 1,; Bannu, *n* = 1,; Dera Ismail Khan, *n* = 1). Three hospitals in Peshawar represent the main urban centers of the province. Two hospitals in Bannu and Dera Ismail Khan cover the southern rural districts, while the Saidu Group of Teaching Hospitals, Swat, represents a semi-urban site serving surrounding rural communities in northern Khyber Pakhtunkhwa. Together, these sites provide a mix of urban and rural populations, reflecting the province’s geographic and socioeconomic diversity. Formal permissions were obtained from the respective hospital administrations to conduct the study at these sites. The selected study areas are given in Fig. 2. In each selected hospital, patients from the urology/nephrology outpatient department (OPD) will be selected based on physician diagnosis.

**Fig. 2 Fig2:**
[figure not shown]
Study area for the current study. DIK Dera Ismail Khan

### Patients’ population and sample size

Participants will include adults (≥ 18 years) with physician-diagnosed uncomplicated UTI who meet all inclusion criteria: (1) confirmed UTI diagnosis, (2) prescribed oral antibiotics (tablet or capsule), (3) having obtained their prescribed medication, (4) willing to participate, and (5) able to provide informed consent.

Patients with polypharmacy (taking five or more medications) [26] are excluded to minimize the risk of confounding factors related to multiple treatment regimens and potential medication interactions that could affect adherence. Patients with complicated UTI (pyelonephritis, sepsis, structural abnormalities) and with multiple comorbidities will be excluded. In addition, patients with cognitive impairment and pregnant or breastfeeding women will also be excluded from the study. Participants may discontinue participation at any time upon request or if they experience clinical deterioration or become ineligible (hospitalization or transfer). All discontinuations and reasons will be documented and summarized in the CONSORT flow diagram.

Eligible uncomplicated UTI patients will be approached during their outpatient visits in the urology department, and written informed consent will be obtained before participation. The patients will be recruited in the current study using the SEAR (Screened, Eligible, Approached, Randomized) framework [27].

The sample size was calculated using R statistical software (version 4.3.0) with “pwr” package (version 1.3.0). Based on our pilot study findings, which demonstrated a 16% improvement in adherence (64.3% in the intervention group vs. 48.3% in the control group), we used this observed effect size (Cohen’s *h* = 0.32) for power calculation. To detect this clinically significant difference in adherence rates with 80% power at a 5% significance level (two-sided test), 152 participants per group (304 total) would be required. Accounting for an estimated 15% attrition rate, informed by our pilot study, we will enroll 179 participants per group (358 total).

### Intervention development

The VISTA intervention was developed using a multi-framework behavioral design grounded in the concept of nudge theory (Fig. 3). Nudge theory, proposed by Thaler and Sunstein in 2008, provided the theoretical foundation and suggested that subtle changes in the way choices are presented or structured can influence the decisions and behavior of people predictably without restricting their freedom of choice [13]. The Taxonomy of Choice Architecture framework [28] was used to systematically categorize the choice architecture techniques, and translated this theory into a practical design strategy by categorizing nudge techniques, such as information simplification and visual reminders, through sticker placement. The messenger, incentives, norms, defaults, salience, priming, affect, commitments, and ego (MINDSPACE) framework complemented these structural techniques by identifying the underlying psychological drivers including credible messenger and affective appeal to enhance engagement and adherence motivation. Together, these frameworks ensured that the VISTA intervention was both theoretically grounded and behaviorally optimized for the context-specific decision-making environment [29].

**Fig. 3 Fig3:**
[figure not shown]
Nudge-based developed intervention sticker. This intervention sticker, designed for antibiotic packaging, visually contrasts non-adherence (up) and adherence (down) to emphasize the consequences of stopping treatment early. The upper panel illustrates how incomplete antibiotic use allows bacteria to evolve into “superbugs,” while the down panel reinforces that completing the full course eradicates infection and protects others. The accompanying illustration “Your choice matters” integrates cultural themes of family protection and social responsibility

The VISTA intervention sticker uses two contrasting scenarios to illustrate the consequences of non-adherence (upper red panel) versus adherence (lower green panel). The red panel depicts bacteria evolving into “superbugs” when treatment is stopped early, while the green panel shows antibiotics fully eradicating bacteria when the full course is completed. The patients in the intervention group will receive this intervention as a sticker on their antibiotic packs.

The intervention was developed in two steps.

#### Step 1: the intervention development using the Delphi method

The Delphi method was used to develop and refine the intervention through iterative rounds of expert feedback [30] and was conducted between November 2024 and February 2025. A total of 40 panelists participated in this step. The panelists were based on clinical expertise (≥ 5 years of experience in treating UTIs), research expertise (published work related to health communication, public health, patient adherence, or antimicrobial resistance), and geographic representation (50% of experts were from Pakistan to ensure feasibility and cultural relevance). Experts were identified through academic databases, professional networks, and snowball sampling.

The process was completed in three rounds (round 1: initial proposal and discussion on the core component of the intervention; round 2: structure feedback and ranking the components of the intervention, based on effectiveness, feasibility, design, and clarity; round 3: final consensus on the intervention regarding design, presentation, and feasibility). An agreement was defined as ≥ 70% of experts rating a component as essential or acceptable [31]. Components that failed to meet the threshold after round 3 were discarded. The details can be seen in Fig. 4.

**Fig. 4 Fig4:**
[figure not shown]
Delphi process for the intervention development (**A**) and panelist participated in the development process (**B**)

#### Step 2: intervention understanding study: patients’ perspective

In this step, the patients’ understanding of the prototype intervention, developed through the Delphi method of step 1, was assessed using a mixed method study design. The study was conducted between March and May 2025. The study participants were adult patients diagnosed with UTI. A total of 30 participants were selected from the outpatient department of tertiary care hospitals, Khyber Pakhtunkhwa, Pakistan.

The quantitative analysis showed that 93.3% of the patients correctly identified the main message of the visual story, highlighting the overall clarity of the intervention (Fig. 5A). Regarding the overall clarity of the intervention visual, 80% of the participants agreed or strongly agreed that the visuals were clear, and 70% stated that there was a clear visual scenario between course completion and incompletion. The details can be seen in Fig. 5B. The demographic analysis showed that 40% of the participants were housewives, 56.7% resided in rural areas, and 20% had no formal education, underscoring that the intervention was a low-literacy-friendly design.

**Fig. 5 Fig5:**
[figure not shown]
Patients’ understanding of the main message (**A**) and visual clarity (**B**) of the intervention

The qualitative analysis identified three main themes: (1) understanding of the visual cues: participants linked non-adherence to stronger germs (e.g., “*Germs grow bigger and redder when pills [antibiotics] are stopped*”), (2) interpretation of symbol: “superbug” was metaphorically understood as weeds, or stubborn goats, (3) cultural and social context: metaphors resonated when tied to daily life (e.g., “*Germs multiply like weeds*”), and social responsibility emerged as a motivator (e.g., “*Finishing pills [antibiotics] protects my family*”). The details are shown in Fig. 6. These insights shaped the intervention’s final design, ensuring clarity, cultural relevance, and behavioral alignment, validating its readiness for the RCT.

**Fig. 6 Fig6:**
[figure not shown]
Thematic analysis of the patient interviews

### Randomization

The participants will be randomly assigned to either the VISTA intervention or control (standard care) groups within each hospital using block randomization. Based on the number of hospitals, a unique randomization list will be generated for each hospital. The block size will be six to ensure balanced allocation within each hospital. The block randomization will be conducted through R using the “blockrand” package. An independent researcher, who has no role in participant recruitment or intervention delivery, will generate the list.

### Allocation

The allocation sequence will be generated by R, and the list will be provided to the data collectors. To ensure allocation concealment, sequentially numbered, opaque, sealed envelopes (SNOSE) will be used, which will be opened only after a participant is deemed eligible and has consented. Personnel responsible for screening and enrollment will not have access to the randomization sequence prior to allocation; only the statistician generating the sequence will have access.

To avoid duplication, the “make answer unique” option will be activated in the Epicollect5 data collection tool. The data will be checked weekly to ensure balance between intervention and control groups, using Microsoft Excel. If there is a minor imbalance (55:45), data collection will continue as block randomization will correct itself over time. However, if there is a major imbalance (70:30), the data collection process audit will be carried out, and if necessary, the randomization list will be regenerated for that hospital.

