### Blinding

The study participants and site staff delivering the intervention will remain unblinded due to the nature of the behavioral intervention. The individual blinded to the intervention assignment will carry out the data analysis using the neutrally labeled data set, such as “group A” and “group B.” To ensure consistent and objective measurement of the outcomes, site staff will receive training to rigorously follow the protocol, and regular monitoring and audits will be conducted to ensure compliance. The physician responsible for patient diagnosis and confirming UTI recurrence will remain blinded to the intervention assignment.

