#### Baseline data

At the start of the study, baseline demographic and patient data will be collected. Additionally, questionnaires regarding knowledge and attitudes will also be collected from all participants. During this stage, patients will be screened based on their prescription filling. Those who filled the prescription will be included for follow-up, while those who did not fill the prescription will be excluded, and the reasons for not filling the prescription will be identified. Data collectors will be trained for intervention implementation and data collection.

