#### Follow-up data

At the follow-up stage, pill counts will measure adherence, and structured questionnaires will be administered to assess changes in knowledge and attitudes regarding antibiotic use. Then, the next follow-up will be done after 1 month, 3 months, and 6 months. At each follow-up, either at the hospital or home visit, the pill count will be performed by the trained data collectors. Returned blister packs will be checked against prescription records. Any discrepancies between the baseline dispensed quantity and the physical count will be documented in site monitoring logs and reviewed by the site supervisor. If packaging is not returned, adherence via pill count will be coded “not verifiable” and treated as missing for the primary pill-count outcome. The details are given in Fig. 8. The overall schedule of enrollment, interventions, and assessments is illustrated in Fig. 9.

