### Ethical considerations

#### Informed consent

Informed consent will be obtained from each participant by a trained data collector at each hospital site, ensuring that they receive a clear explanation of the study’s purpose (improving antibiotic adherence through VISTA intervention), procedures (randomization, intervention delivery, follow-up visits for pill counts, and questionnaire survey), and potential risks and benefits. Participants will be explicitly assured that their participation is entirely voluntary, and they retain the right to withdraw from the study at any time without penalty or impact on their medical care. Additionally, the consent process will describe data anonymization measures, such as replacing personal identifiers with unique codes, and confidentiality safeguards, including secure storage of data and restricted access to authorized study personnel only.

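### The Allocation section contradicts itself on who may see the randomization list: it gives the list to the data collectors, who take consent, and then reserves it to the statistician

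*Protocol article*

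**What the plan says.** Two sections of the protocol article set out the procedure. Under Randomization, an independent researcher with no part in recruitment or delivery generates a separate list for each hospital, in blocks of six. Under Allocation, three statements follow one another:

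- "The allocation sequence will be generated by R, and the list will be provided to the data collectors".
- Concealment rests on numbered, opaque envelopes that stay sealed until eligibility and consent are settled.
- "Personnel responsible for screening and enrollment will not have access to the randomization sequence prior to allocation". The rest of that sentence reserves the sequence to the statistician who produced it.

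Other sections say what data collectors do:

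- Informed consent: "Informed consent will be obtained from each participant by a trained data collector at each hospital site".
- Baseline data: "Data collectors will be trained for intervention implementation and data collection".
- Follow-up data: at each follow-up, "the pill count will be performed by the trained data collectors". This count is the primary outcome measure.

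The Blinding section adds: "The study participants and site staff delivering the intervention will remain unblinded due to the nature of the behavioral intervention".

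**The concern.** Allocation concealment protects the interval between meeting a patient and committing that patient to the trial. The person who takes consent acts in exactly that interval. Here that person is a data collector, and data collectors are also the group said to receive the list.

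Someone who knows the next arm can choose when to approach a patient, or can put more or less effort into the consent discussion, according to how adherent the patient seems. Adherence is the primary outcome, so selection of this kind would enter the treatment comparison directly. The planned adjustment for baseline characteristics (age, sex, poverty category and education are the examples given) cannot be relied on to remove it, because a recruiter's impression of a patient is not among those variables. The Discussion counts randomization among the means of minimizing bias, and randomization does that only if allocation is concealed.

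**Working it through.** The plan gives no figure for concealment, so the main check is to set the statements side by side.

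**Step 1. Can the Allocation statements all be true?**

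| Statement | Who has the list or sequence |
|---|---|
| First sentence of Allocation | The data collectors |
| Concealment sentence, first half | Not the screening and enrollment staff, before allocation |
| Concealment sentence, second half | The generating statistician only |

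The first and third rows are incompatible whatever else data collectors do: if they are given the list, the statistician is not its only holder.

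**Step 2. Are data collectors enrolling staff?** Yes, on the strength of consent alone. The envelope is opened only after eligibility and consent, and a data collector takes the consent. The first and second rows therefore also conflict if the handover comes before allocation. The article gives no timing, and it describes no separate group of data collectors who hold the list but do not recruit.

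**Step 3. How foreseeable is allocation with and without the list?** Inputs: 1:1 ratio (Study design), fixed blocks of six within hospital (Randomization), 358 participants (Patients' population and sample size). The last figure reproduces: 152 / (1 − 0.15) = 178.8, rounded up to 179 per group, and 2 × 179 = 358.

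- *No information:* 50% of guesses are correct.
- *No list, but staff know the block size and recall every earlier allocation at their hospital (assumption):* there are C(6,3) = 20 possible blocks. Always guessing the arm with more places left in the block gives, with m = 3, an expected m + 2^(2m−1)/C(2m,m) − 1/2 = 3 + 32/20 − 0.5 = 4.1 correct of 6, or 68.3%. The number of allocations known with certainty is on average 2m/(m+1) = 6/4 = 1.5 of 6, or 25%. Enumerating all 20 blocks gives the same two results.
- *Readable list before allocation:* 6 of 6, or 100%, hence up to all 358.

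A readable list would therefore raise the share of allocations known with certainty from 25% to 100%, even against well-informed guessing.

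**Step 4. Does any planned figure change?** No. Sample size, significance level and power do not depend on this point.

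**The case against.** The best case on the other side is that the first sentence is loose wording. The sentences that follow it are specific and correct: sealed, opaque, numbered envelopes, opened late, with no access for enrolling staff. The list is generated independently. The authors may simply have meant that the list reaches the sites inside the envelopes, or that data collectors see a record of allocations already made. Both are plausible, and nothing in the article shows that a readable list was released. This part of the objection stands, and it limits the conclusion to a contradiction with a conditional consequence. It does not rescue the text: neither meaning is written, and a site that followed the sentence literally would give up concealment. Nor is this a detail left to a fuller protocol, since the article itself states two incompatible procedures.

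A reader might infer three stronger things that the documents do not support:

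- *That data collectors deliver the sticker.* They are trained for implementing the intervention, and unblinded site staff deliver it, but no sentence says who affixes it. The contradiction does not need this.
- *That data collectors can steer borderline exclusions such as multiple comorbidities or cognitive impairment.* The article does not say who makes those judgements. Diagnosis lies with a physician who is blinded to assignment.
- *That data collectors who hold the list and data collectors who take consent must be the same individuals.* The Data collection procedure section describes teams of data collectors at various sites. The text neither separates the two tasks nor says that one person does both.

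**Conclusion.** The Allocation section is wrong as written and must be corrected. It names two incompatible holders of the list, and one of them is the group that takes consent. That conclusion rests on the text alone.

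The consequence is conditional. If the list is readable before allocation, every upcoming allocation is foreseeable and the envelopes no longer conceal it. If it never was, this is an error of wording on a point central to the trial's validity. A reader might conclude outright that the envelopes are defeated; the documents do not support that, because they give neither the timing nor the form of the handover.

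A reader might also want to put a figure on the bias. It would be the share of places steered, multiplied by the gap in expected adherence between steered and typical patients. The documents give neither quantity, so the size is unknown and could be zero. The 68.3% and 25% above describe predictability under stated assumptions about staff knowledge; they do not measure bias.

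**What to change.** 1. In Allocation, delete the second clause of the first sentence, which gives the list to the data collectors.
2. State that the independent generator alone holds the list. Use one title for this person, who is called a researcher under Randomization and a statistician under Allocation (taken here to be the same person).
3. State that sites receive only sequentially numbered, opaque, sealed envelopes, opened after eligibility and consent, and that used envelopes are reconciled to the list centrally.
4. Trial status gives August 06, 2025 as the start of recruitment and anticipates its completion on September 30, 2025. A change of wording therefore cannot restore concealment for anyone already enrolled. Establish from each of the six hospitals whether any data collector received a readable list and, if so, report which participants were enrolled under it.

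Items 1 to 3 cost a short amendment and an instruction to sites; the independent generator is already in the plan. Item 4 costs an enquiry at six sites and a statement in the trial report. The fix does not remove the weaker, separate predictability that comes from a fixed, published block size with unblinded staff.
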